### Blinding

The specific nature of the intervention makes it impossible to blind the acupuncturist. However, the participants, data collection staff, and data analysts will be blinded. To maximize blinding of participants, placebo needles and sham electroacupuncture design will be used in the sham-electroacupuncture group. Adhesive pads will be applied to both EA and SEA groups to ensure that the participants are unaware of the differences between the two acupuncture treatments. Each participant will receive intervention in a personal space separated by bed curtain and no communication will be allowed between participants. During the intervention period, the acupuncturist and the data collection researcher will not be allowed to exchange information on grouping, treatment procedures, and outcomes. Blinded evaluation and blinded statistical analysis will be emphasized during the data collection and analysis stage.

### Interventions

#### Study flow

The treatments will be performed by one licensed acupuncturist who has at least 5 years of experience with acupuncture. All participants will be treated in supine position on the treatment couch. Treatment will be conducted during three menstrual cycles, at a frequency of 3 sessions per week (once every 2–3 days) in both intervention and control groups after randomization with each group receiving 30 min per session. If a woman becomes pregnant during the intervention phase, the intervention will be terminated. Six months after completion of the treatment, follow-up will be performed by telephone or WeChat to ask if the participants are pregnant.

#### Electroacupuncture (EA) group

To improve endometrial receptivity in infertile patients with thin endometrium, electroacupuncture prescription will be developed based on clinical practice and literature review. The obligatory acupoints will include bilateral Tianshu (ST25), Zigong (EX-CA1), Sanyinjiao (SP6), Guilai (ST29), individual Zhongji (RN3), and Guanyuan (RN4). Additionally, sets of adjunct acupoints will be alternately selected by the acupuncturists based on the periodic therapy of Traditional Chinese Medicine: bilateral Xuehai (SP10) and Diji (SP8) will be needled during menstruation; bilateral Taichong (LR3) and Taixi (KI3) will be needled after menstruation; bilateral Taichong (LR3), Hegu (LI4), and Zusanli (ST36) will be needled during the ovulatory period; individual Qihai (RN6) and bilateral Zusanli (ST36) will be needled before the next menstruation. Acupuncture points will be identified according to the method of point location issued by the World Health Organization. Stick adhesive pads (15 mm) will be placed at all points. After sterilization of the skin with alcohol wipes, single-use, stainless, sterile needles (gauge 0.25 × 40 mm or 0.25 × 60 mm; Hwato, Suzhou, China) will be needle inserted.

In a supine position, the needle will be inserted 40 mm vertically into the muscles of the abdominal wall through the pads for ST25, ST29, RN4, and RN3. EX-CA1 and RN6 will be inserted vertically to a depth of 25 mm in the abdomen. The needle will then be inserted vertically at SP6, SP10, and SP8 to a depth of 25 mm. LR3 will be punctured vertically to a depth of 15 mm into the skin, while LI4 and ST36 will be punctured perpendicularly to a respective depth of 25 mm and 40 mm, respectively. Deqi sensation (including numbness, soreness, distention, heaviness) will be achieved through lifting, thrusting, and rotating for 10 s on each point. An electric stimulator (HANS-200E acupoint nerve stimulator, Nanjing Jisheng Medical Co, Ltd) will be applied to bilateral ST25 and ST29 with disperse-dense waves of 2/100 Hz frequencies for 30 min. The current intensity will be increased until the needles start vibrating slightly. After a 30-min retention period, all needles, electrode clamps, and stick adhesive pads will be removed.

#### Sham-electroacupuncture (SEA) group

Participants in the sham electroacupuncture group will receive sham EA on therapeutic acupoints without skin penetration or electrical stimulation [38]. The procedures, frequency, and duration of treatment will be the same as that of the electroacupuncture group. Blunt needles which are similar to Streitberger needles device will be used [39]. This type of needle can provoke a needling sensation quite similar to real acupuncture as soon as it touches the skin, without insertion. The acupuncturists should pretend to manipulate the needles slightly with an even lifting, thrusting, and twisting method for 10 s on each point as well. No Deqi sensation will be induced. Similarly, the needles on bilateral ST25 and ST29 will be connected to a sham electric stimulator with the same parameters as the EA group, but the wire will be cut thus no current intensity. The light seen and the sound of the pulse generator heard will be the same as the EA group.

### Outcome measures

#### Primary outcome

The primary outcome will be endometrial thickness in the mid-luteal phase of the 3rd menstrual cycle (the primary time frame), the 1st menstrual cycle and 2nd menstrual cycle as well as 6 months after completion of the treatment (the secondary time frame) compared with baseline (in the − 1st menstrual cycle).

#### Secondary outcome measures

The secondary outcomes include the following four aspects: (1) endometrial pattern, (2) RI and PI of bilateral uterine artery and endometrium blood flow, (3) serum estradiol (E2) and progesterone (P), and (4) pregnancy rate. The first three of the secondary outcomes will be evaluated in the mid-luteal phase of 3rd menstrual cycle (the primary time frame) and the 1st menstrual cycle and 2nd menstrual cycle, as well as 6 months after treatment (the secondary time frame) in comparison with the baseline (in the − 1st menstrual cycle). The pregnancy rate will be assessed during a 6-month follow-up after completion of the trial.

A certified sonographer will measure the endometrial thickness and the first three secondary outcomes through transvaginal ultrasound. A laboratory physician will test the serum estradiol and progesterone through radioimmunoassay. They will be trained and assessed before the trial.

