The endometrium, a unique cyclic tissue regeneration system, depends on the cyclical growth and regression of blood vessels that supply the endometrium [19]. Previous works showed that angiogenesis which depends on the expression of angiogenic factors (VEGF, FGF, and angiopoietin families) is a critical factor in determining the endometrial receptivity during the implantation window (IW) [20]. Thin endometria are characterized by high uterine blood flow impedance, poor growth of glandular epithelium, decreased expression of vascular endothelial growth factor (VEGF), and poor vascular development [21]. Current therapeutic strategies for thin endometrium include long-term administration of exogenous estrogen, low-dose of aspirin, vaginal sildenafil citrate application, transvaginal endometrial perfusion of granulocyte colony-stimulating factor (G-CSF), autologous platelet-rich plasma infusion (PRP), stem cell therapy, vitamins C and E, and L-arginine supplement [8, 22]. Despite the vast diversity of treatment, most of these treatment options result in a minor change in the endometrium thickness and pregnancy rate [22]. Currently, there is no one acceptable approach to treat thin endometrium [23], thus the need for an alternative and complementary therapy for patients with thin endometrium.

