#### Sample size

There is insufficient previous data on endometrial thickness after treatment with EA in infertile women with thin endometrium. Besides, the effect of acupuncture varies with different acupoint selection. The aim of the research was to clarify the effects of EA on thin endometrium in infertile women. Therefore, the change in endometrial thickness will be used as an evaluation index. Based on our pilot study, changes in endometrial thickness of the mid-luteal phase after a 12-week treatment were shown to be 8.30 ± 2.83 mm (*n* = 10) in the electroacupuncture group (EA) and 7.10 ± 1.97 mm (*n* = 9) in the sham electroacupuncture group (SEA). Measurement data of parallel control trials (1:1) will be analyzed statistically using the following formula for sample size estimation:
$$ n=\frac{{\left({Z}_{\alpha }+{Z}_{\beta}\right)}^2\ast 2{\sigma}^2}{\delta^2} $$

With a 5% significance level (*α* = 0.05, two-sided) and 80% power (*β* = 0.2), at least 62 patients should be enrolled in each group and a total of 142 participants will be recruited to allow for a 15% dropout rate.

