#### Statistical analysis

Statistical analyses of data will be performed using SPSS21.0 software (International Business Machines Corp., Armonk, NY) by analysts who will be blinded to the patients’ allocation. To evaluate the curative effect in this trial, an intention-to-treat analysis (ITT) will be performed. Categorical variables will be presented by frequency (percentage) and analyzed with the chi-squared test or Fisher’s exact test. Continuous variables will be presented as mean ± standard deviation (M ± SD) if they meet normal distribution. Otherwise, they will be presented as medians ± interquartile range (M ± IQR). The demographic characteristics will be compared between the groups by independent *t* tests at baseline. All longitudinal analyses for continuous variables measured at baseline and three-time periods will be performed using linear mixed modeling. Comparisons between the intervention and control groups will be performed using the chi-square test or Fisher s exact test, as appropriate, for categorical variables. To evaluate the safety of acupuncture, we will use a Fisher exact test to report the relative risk of an adverse effect. All the tests will be two-sided, and a *P* value of less than 0.05 will be considered to be statistically significant.

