### Outcome measures selection

Endometrial receptivity plays a vital role in embryo-endometrium cross talk. Endometrium exhibits a short period of receptivity, known as the “window of implantation” [2]. The IW appears in the mid-secretive phase of endometrium on the 20th to 23rd day in the menstrual cycle (namely the 7th–9th day after ovulation) [52]. Therefore, markers of endometrial receptivity are tested in the mid-luteal phase (7 days after the day of ovulation) for a natural menstrual cycle in clinical practice. The ultrasound markers for evaluation of endometrial receptivity are endometrial thickness, pattern, and blood flow impedance [5]. Endometrial thickness as an essential factor in endometrial receptivity is the most extensively used method in clinical practice [53, 54]. Previous research showed a positive correlation between endometrial thickness and implantation rates in 465 cycles of oocyte donation [55]. Endometrial blood perfusion is an important factor for endometrial growth [56]. Resistance and pulsatility index of subendometrial and uterine artery are useful tools for clinicians in predicting endometrial receptivity [57]. High blood flow impedance of uterine radial arteries is associated with poor endometrial growth in patients with thin endometrium [21]. The diastolic flow of the uterine artery in the mid-luteal phase is also associated with reproductive success [58]. Endometrial blood flow directly reflects the microenvironment of embryo implantation. Successful intrauterine implantation is positively associated with lower subendometrial resistance index (RI) and pulsatility index (PI) [59]. In the study, endometrial blood perfusion will be assessed using the PI and RI of bilateral uterine artery as well as endometrium blood flow. The endometrial patterns including type A (triple-line), type B, and type C is classified according to morphology of the endometrium [60]. An earlier study showed that the presence of a triple-line endometrium with a thickness > 6 mm was strongly correlated with conception [61]. The triple line pattern assessed on the day of HCG injection OR IUI was associated with higher clinical pregnancy rates [54]. The endometrium undergoes complex changes in the circulation of estrogen and progesterone (P), which culminate at the mid-luteal phase of the menstrual cycle when it becomes receptive [2, 62, 63]. Serum estradiol and progesterone concentrations may reflect endometrial status [64]. Estradiol stimulates both increases in the size and number of myometrial and endometrial cells as well as changes in endometrial thickness [64]. It is noteworthy that there is a minimum concentration of progesterone which is required to induce normal secretory endometrial development and receptivity [65]. This is supported by a previous study which revealed a significant decrease in clinical pregnancy and live birth rate with serum progesterone level < 10 ng/ml [66].

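### RI and PI of endometrial flow exist only where flow is detected, so the arm comparison on this secondary outcome can be biased, in a direction and by an amount the documents do not settle

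*Protocol article*

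**What the plan says.** Under Secondary outcome measures, the protocol article names "RI and PI of bilateral uterine artery and endometrium blood flow", measured by transvaginal ultrasound at baseline, in cycles 1 to 3 and six months after treatment, with cycle 3 as the main time point. Under Outcome measures selection it repeats that "endometrial blood perfusion will be assessed using the PI and RI of bilateral uterine artery as well as endometrium blood flow". It names no measure of whether endometrial flow was present. The same section associates lower subendometrial values with successful implantation, so lower is better.

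The Background says of the population under study: "Thin endometria are characterized by high uterine blood flow impedance, poor growth of glandular epithelium". The same sentence adds poor vascular development.

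Under Statistical analysis: "All longitudinal analyses for continuous variables measured at baseline and three-time periods will be performed using linear mixed modeling". That section also says that "an intention-to-treat analysis (ITT) will be performed". The article does not say what is recorded or analysed when no endometrial waveform is obtained.

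**The concern.** RI and PI are ratios built from blood-flow velocities, and without a waveform there is nothing to calculate. A woman scanned as planned can therefore lack an endometrial RI and PI because her perfusion is poor, and not because she missed the visit.

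A linear mixed model uses the values it has. It is valid when the chance of a gap depends only on values already observed. Here the gap may depend on the very impedance that could not be measured. If EA changes perfusion, as the article hypothesises, the arms will also differ in who has a value. The comparison is then between two differently selected groups of women. Declaring intention to treat does not supply the missing values.

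At stake is the reading of one component of one secondary outcome. A change from no flow to detectable flow would enter the model only as a new, possibly high, RI or PI, with no earlier value to set it against.

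**Working it through.** **The plan's own figures.** There is none for this outcome: no detection rate, no expected RI/PI effect and no SD. The only sizing concerns endometrial thickness. With the plain average of the pilot SDs, (2.83 + 1.97)/2 = 2.40 mm, and a difference of 8.30 − 7.10 = 1.20 mm, n = 2 × (1.960 + 0.842)² × 2.40²/1.20² = 62.8 per group, against 62 stated. This has no bearing on the point.

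**Inputs, all assumed.** Latent endometrial impedance is standard normal in sham, higher being worse. EA lowers it by 0.5 SD. A share q of sham women have no detectable flow, with q = 5%, 10%, 20% or 30%.

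**A. Uniform benefit, sharp limit.** Flow is undetected above c, where Φ(c) = 1 − q. Among women with a value:
- sham mean = −φ(c)/Φ(c)
- EA mean = −0.5 − φ(c + 0.5)/Φ(c + 0.5)

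For q = 30%, c = 0.524. The sham mean is −0.497 and the EA mean −0.779, a difference of −0.282 against a true −0.500, ratio 0.56. Undetected in EA: 15%.

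A baseline-adjusted version (ANCOVA in women with values at both visits, assumed baseline correlation 0.6, by simulation) stands in for the planned model, which also uses earlier readings. It is an approximation to that model.

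**B. Uniform benefit, loose detection.** Detection depends on impedance plus independent noise of SD 2, so the total SD is √5 = 2.236. The selection terms are divided by 2.236, and the EA limit moves by 0.5/2.236 = 0.224. For q = 30%: sham −0.222, EA −0.674, difference −0.452, ratio 0.90.

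**C. No response in women without flow.** Women who would lack flow at cycle 3 gain nothing; the others gain 0.5 SD. The true mean effect is 0.5 × (1 − q), the observed effect among women with a value is 0.5, and the ratio is 1/(1 − q). For q = 30%: 0.50/0.35 = 1.43.

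Ratio of observed to true effect:

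| Undetected in sham | A, unadjusted | A, baseline-adjusted | B, unadjusted | C |
|---|---|---|---|---|
| 5% | 0.86 | 0.92 | 0.97 | 1.05 |
| 10% | 0.78 | 0.87 | 0.95 | 1.11 |
| 20% | 0.66 | 0.79 | 0.92 | 1.25 |
| 30% | 0.56 | 0.73 | 0.90 | 1.43 |

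**Between A and C** (unadjusted, sharp limit, 10% to 30% undetected). If women who would lack flow gain half the benefit, the ratio is 0.90 to 0.84; if a quarter, about 0.99 to 1.08. If non-response instead follows absent flow at baseline, the ratio over 5% to 30% is 0.91 to 0.84 unadjusted and 0.97 to 1.04 baseline-adjusted. Both sign and size therefore turn on how the poorly perfused women respond and how tightly detection follows impedance.

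**The case against.** Nothing in the article says that endometrial flow goes undetected in any woman. High impedance is a high, measurable RI or PI, not an absent waveform, and the Discussion treats subendometrial indices as usable clinical markers. If detection is close to complete, there is no problem. This stands: the step from high impedance to no value is plausible for endometria described as poorly vascularised, but its frequency is unknown.

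The article is also a condensed account. A rule for unobtainable waveforms may sit in the full protocol, the scanning procedures, the case report form or the SAP, none of which is shown. This too stands, so the silence is not itself an error. What the article does fix is the form of the outcome, RI and PI only, and the model. Whether flow was detected must be noted at the scan, because a later plan cannot tell a blank for no flow from a blank for a missed scan.

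A reader might go further and infer that a real benefit of EA is understated, by as much as 44% (1 − 0.56) with 30% undetected. The documents do not support that. The figure is for an unadjusted comparison with a sharp limit and the same benefit in every woman; baseline adjustment alone reduces the loss to 27% (1 − 0.73). If the women without flow do not respond, the benefit is overstated. Material overstatement does need almost no response in those women, so understatement may be the likelier direction, but that is a judgement about responses on which the documents are silent.

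**Conclusion.** The point holds as a possible bias of unknown direction and size in the endometrial RI/PI comparison. It rests on two conditions: some women have no detectable endometrial flow, and this is related to their perfusion. The first is not documented; the second is plausible from the article's description of the population. Under the assumed 0.5 SD benefit and 5% to 30% undetected in sham, the observed effect could be anywhere from 0.56 to 1.43 of the true one across the three scenarios, and close to 1 if detection is nearly complete or only loosely tied to impedance.

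The uterine artery RI and PI are not drawn in, since nothing in the documents suggests that their waveforms would be missing. Endometrial thickness and the sample size are untouched. This is a worthwhile refinement of one secondary outcome and does not threaten the trial's main conclusion.

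**What to change.** - At each scan already scheduled, record endometrial flow as detected, not detected, or not assessable for technical reasons.
- Report the proportion with detectable endometrial flow by arm.
- Keep the mixed model for uterine artery RI and PI. Keep it for endometrial RI and PI too, but state that it describes women with detectable flow.
- Add, as a supporting analysis, a cycle-3 comparison that ranks no detectable flow as the worst value and so keeps the scanned women without flow in the comparison. Technically unassessable scans should be treated as missing, not ranked worst.

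The cost is one case report form item and one extra secondary analysis. That analysis gives a rank comparison and not a mean difference, does not use the repeated readings, and assumes that non-detection means the poorest perfusion; the third recording category limits that last weakness. Replacing the planned model outright is not warranted while the detection rate is unknown. If detection proves nearly complete, the results will hardly change.

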**Methods:**

This study is a randomized, single-blinded, controlled, clinical trial. A total of 142 eligible patients will be recruited and randomly assigned to the electroacupuncture (EA) group or the sham electroacupuncture (SEA) group in a 1:1 ratio. Participants will receive 36 sessions over three menstrual cycles (12 weeks in total), with the same acupoint prescription. The primary outcome of this trial is endometrial thickness in the midluteal phase. The secondary outcomes include endometrial pattern, resistance index (RI) and pulsatility index (PI) of bilateral uterine artery and endometrium blood flow, serum estradiol (E2) and progesterone (P), and pregnancy rate. The pregnancy rate will be evaluated during a 6-month follow-up after completion of the trial. All other outcomes will be evaluated before treatment, during the treatment of 1st, 2nd, and 3rd menstrual cycle, and 6 months after treatment.

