### Inclusion criteria

Patients who conform to the following criteria will be included:
Females, aged between 20 and 45 years;Meets the diagnosis of infertility and is trying to conceive;EMT < 7 mm in the midluteal phase;Willing to participate in this study and sign an informed consent form.

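### The pregnancy-rate window is set in two different ways, and neither counts every pregnancy from randomisation; read literally, the stated window understates an effective treatment

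*Protocol article*

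**What the plan says.** Two places in the protocol article tie the pregnancy rate to a period after the trial. Secondary outcome measures has "The pregnancy rate will be assessed during a 6-month follow-up after completion of the trial", and the Methods paragraph of the Abstract has "The pregnancy rate will be evaluated during a 6-month follow-up after completion of the trial". The Abstract then sets pregnancy apart from everything else: "All other outcomes will be evaluated before treatment, during the treatment of 1st, 2nd, and 3rd menstrual cycle, and 6 months after treatment".

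Study flow describes the measurement differently. There is one contact, six months after the treatment is completed, at which "follow-up will be performed by telephone or WeChat to ask if the participants are pregnant". The same section foresees conception on treatment: "If a woman becomes pregnant during the intervention phase, the intervention will be terminated". It says what happens to the intervention, but not how the pregnancy is counted.

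Two other statements bear on the point. An inclusion criterion reads "Meets the diagnosis of infertility and is trying to conceive". Under Statistical analysis, "an intention-to-treat analysis (ITT) will be performed".

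**The concern.** Treatment lasts three menstrual cycles, 12 weeks, in women who want to conceive. If EA works, some of the women it helps will conceive in those cycles. Under the window in the Abstract and in Secondary outcome measures, taken at its word, such a woman is not an event. She remains in the intention-to-treat denominator, and while pregnant she cannot conceive in the period that is counted. The better the treatment works early, the more of its successes are recorded as failures.

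The Study flow question has a different weakness. Asking whether a woman is pregnant at month 6 records a state on one day. A pregnancy that began and ended before that day is lost, and the Background itself links thin endometrium to more spontaneous abortion and ectopic pregnancy.

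Pregnancy is the trial's only direct fertility outcome, so its definition should not be open to two readings with different answers.

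**Working it through.** **No figure to reproduce.** The protocol gives no expected pregnancy or conception rate. Its sample size rests on endometrial thickness and does not enter here.

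**Inputs from the protocol.** Three treatment cycles in 12 weeks, so about 4 weeks per cycle (Abstract); 6 months of follow-up (Abstract, Secondary outcome measures, Study flow); 142 women randomised 1:1, so 71 per arm (Sample size); intention to treat and two-sided 5% tests (Statistical analysis).

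**Assumptions.** A per-cycle conception probability *p_t* in treatment cycles and *p_f* in follow-up cycles, the same for all women in an arm; six follow-up cycles; no losses.

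**Formulas, all randomised women in the denominator.**
- Literal window: L = (1 - p_t)^3 × [1 - (1 - p_f)^6]
- From randomisation: C = 1 - (1 - p_t)^3 × (1 - p_f)^6

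**Sham at 5% throughout.** 0.95^3 = 0.857 and 0.95^6 = 0.735. L = 0.857 × 0.265 = 22.7%. C = 1 - 0.857 × 0.735 = 37.0%.

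**EA at 10% on treatment** (0.9^3 = 0.729), with three assumptions about what follows. Differences are taken before rounding.

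| EA rate in follow-up | L, EA | L, EA - sham | C, EA | C, EA - sham |
|---|---|---|---|---|
| 10% (effect persists) | 0.729 × 0.469 = 34.2% | +11.4 | 1 - 0.729 × 0.531 = 61.3% | +24.3 |
| 7.5% (half retained) | 0.729 × 0.374 = 27.2% | +4.5 | 1 - 0.729 × 0.626 = 54.3% | +17.4 |
| 5% (treatment only) | 0.729 × 0.265 = 19.3% | -3.4 | 1 - 0.729 × 0.735 = 46.4% | +9.4 |

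**Lower rates, 5% against 3% on treatment.** Sham: L = 0.913 × 0.167 = 15.2%, C = 24.0%. If the effect persists, EA has L = 22.7% (+7.5) and C = 37.0% (+13.0). If it stops with treatment, EA has L = 0.857 × 0.167 = 14.3% (-0.9) and C = 28.6% (+4.6).

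**Wider range, sham 2% to 20% per cycle, EA 1.5 to 3 times as high on treatment.**
- Effect on treatment only: the literal window reverses in every case, from -0.3 to -33 points, while the count from randomisation favours EA by +2.5 to +20.6.
- Half retained: no reversal at sham rates of 5% or less; reversal at 8% with a ratio of 3, and at 10% or more.
- Fully retained: no reversal at 8% or less, nor at 10% with ratios of 1.5 to 2; reversal at 10% with a ratio of 3, and at 15% to 20%.

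**Power with 71 per arm, persistent case (10% against 5%).** Power = Φ[(Δ - 1.96 SE0)/SE1], with SE0 from the pooled and SE1 from the separate proportions.
- Literal window: (0.1145 - 1.96 × 0.0757)/0.0751 = -0.45, power 33%.
- From randomisation: (0.2428 - 1.96 × 0.0839)/0.0814 = 0.96, power 83%.

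**If on-treatment conceptions also left the denominator.** The treatment-only case gives 26.5% in both arms: no reversal, but the benefit disappears.

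**The month-6 question.** Taking 6 months as 26 weeks, the contact falls at week 12 + 26 = 38. A mid-cycle conception in treatment cycle 1 (week 2) is then 36 weeks old; in cycles 2 and 3, 32 and 28 weeks. Most on-treatment pregnancies still ongoing could therefore be reported. Those that had ended could not.

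**The anchors.** The Abstract and Secondary outcome measures count from the end of the trial, Study flow from the end of treatment. For a woman whose treatment is stopped for pregnancy, the end of treatment also comes early, so an individual anchor could differ by arm.

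**The case against.** The strongest reply is that nothing in the article says on-treatment conceptions are excluded. Saying that the rate is assessed during follow-up may describe when pregnancy is ascertained, not which conceptions qualify, and the month-6 question would pick up most that are still ongoing. This stands. A reader might infer that the protocol has decided to leave these pregnancies out; the text does not support that. The two weaknesses are alternative readings and should not be added together.

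Second, a reader might infer that the comparison will reverse. Reversal needs an effect that fades after treatment or fairly high conception rates, and the documents give neither. With a persistent effect and low conception rates the result is attenuation only. This also stands.

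Third, a reader might say that the randomised comparison is discarded. It is not, if all randomised women stay in the denominator as the intention-to-treat statement implies; the fault is then that events are coded as non-events.

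Fourth, this is a condensed article, its schedule table is not shown, and counting rules may sit in the case report form or analysis plan. That would answer a complaint about missing detail. It does not answer this point, which rests on what the article states: a window given twice, and a different measurement given once. Neither yields cumulative pregnancy from randomisation.

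**Conclusion.** The point holds as an outcome that is badly fixed and inconsistently described. On the literal window, an effective treatment's benefit is understated in every scenario examined. With 10% against 5% per cycle it falls from +24.3 to +11.4 points if the effect persists, and from +9.4 to -3.4 if the effect is confined to treatment. These sizes rest on assumed conception rates, equal fecundity within each arm, six follow-up cycles and no losses. On the Study flow reading the loss is limited to pregnancies that ended before the contact; it is probably smaller and cannot be sized from the documents.

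This should be fixed, but it does not threaten the trial's main conclusion. Pregnancy is the last of four secondary outcomes, and neither the endometrial-thickness comparison nor the sample size depends on it.

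**What to change.** Define the pregnancy rate as the proportion of all randomised women with at least one pregnancy starting between randomisation and six months after the end of the planned treatment period, on the same clock in both arms. State that conceptions during treatment are events, including those that led to the intervention being stopped. Use this one anchor in the Abstract, Study flow and Secondary outcome measures.

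At the month-6 contact, ask whether the woman has been pregnant at any time since randomisation and when each pregnancy began, and combine the answers with pregnancies recorded during treatment.

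The cost is one sentence in the outcome definition, matching wording in the other two places, and a change to the telephone or WeChat question. No extra visit or participant is needed, and on-treatment pregnancies should already be known because they end the intervention.
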